## Abstract

**Background:**

Physical activity alleviates chronic stress. The latest research suggests a relationship between resilience and physical fitness. Beneficial adaptations of the hypothalamic-pituitary-adrenal axis, sympathetic nervous system, endocannabinoid system, and tryptophan pathway, which are induced by an active lifestyle, are considered to be conducive to resilience. However, detailed knowledge on the molecular link between the effects of acute and chronic physical exercise and improved resilience to stress in humans is missing. Moreover, the relationship between innate and acquired aerobic capacity and resilience is poorly understood.

**Objective:**

The aim of this study is to implement a human exercise intervention trial addressing the following main hypotheses: a high innate aerobic capacity is associated with high resilience to stress, and web-based physical exercise training improves aerobic capacity of physically inactive adults, which is accompanied by improved resilience. In this setting, we will analyze the relationship between resilience parameters and innate and acquired aerobic capacity as well as circulating signaling molecules.

**Methods:**

A total of 70 healthy, physically inactive (<150 minutes/week of physical activity) adults (aged 18-45 years) will be randomly assigned to an intervention or control group. Participants in the intervention group will receive weekly training using progressive endurance and interval running adapted individually to their remotely supervised home training performance via web-based coach support. A standardized incremental treadmill exercise test will be performed before and after the intervention period of 8 weeks to determine the innate and acquired aerobic capacity (peak oxygen uptake). Before and after the intervention, psychological tests and questionnaires that characterize parameters implicated in resilience will be applied. Blood and saliva will be sampled for the analysis of cortisol, lactate, endocannabinoids, catecholamines, kynurenic acid, and further circulating signal transducers. Statistical analysis will provide comprehensive knowledge on the relationship between aerobic capacity and resilience, as well as the capacity of peripheral factors to mediate the promoting effects of exercise on resilience.

**Results:**

The study was registered in October 2019, and enrollment began in September 2019. Of the 161 participants who were initially screened via a telephone survey, 43 (26.7%) fulfilled the inclusion criteria and were included in the study. Among the 55% (17/31) of participants in the intervention group and 45% (14/31) of participants in the control group who completed the study, no serious adverse incidents were reported. Of 43 participants, 4 (9%) withdrew during the program (for individual reasons) and 8 (19%) have not yet participated in the program; moreover, further study recruitment was paused for an indeterminate amount of time because of the COVID-19 pandemic.

**Conclusions:**

Our study aims to further define the physiological characteristics of human resilience, and it may offer novel approaches for the prevention and therapy of mental disorders via an exercise prescription.

**International Registered Report Identifier (IRRID):**

DERR1-10.2196/29712

## Introduction

### Background

Physical inactivity is one of the major risk factors for global mortality; therefore, an active lifestyle is highly important to promote health and longevity. The risk for cardiovascular diseases, type 2 diabetes, osteoporosis, metabolic syndrome, specific cancers, and several other diseases is reduced by being physically active [1], and physical exercise can be prescribed as a medicine for 26 common chronic diseases [2]. In addition, mental health is positively affected by regular physical activity. Physical exercise induces the preservation of brain volume, which is associated with cognitive benefits [3,4]; it promotes blood-brain barrier integrity and protects against central nervous system infiltration of immune cells [5], and neurodegenerative diseases, such as Alzheimer and Parkinson disease, are counteracted by an active lifestyle [6].

To show the influence of exercise type, frequency, duration, and intensity on mental health, a cross-sectional study was conducted with 1.2 million individuals in the United States between 2011 and 2015 [7]. It was shown that regularly physically active persons have approximately half as many days of poor mental health than physically inactive persons. Furthermore, it was demonstrated that any kind of exercise had a reduced mental health burden compared with not exercising. A duration of at least 45 minutes with a frequency of 3 to 5 times a week is recommended. However, the authors also cautioned that more exercise is not always better [7].

To improve peak oxygen uptake (VO_2_peak), it has been shown that individuals who perform interval training have a higher increase in VO_2_peak [8] or have a shorter exercise duration with similar increases in VO_2_peak compared with those who perform continuous exercise [9-11]. The comparison between low- and high-fit groups showed that the high-fit participants reacted and recovered faster within and after a psychological stress situation [12,13]. Furthermore, high-fit individuals had a lower cortisol concentration at rest and higher variability during the stressor compared with low-fit individuals. Moreover, a low cardiorespiratory fitness at the age of 18 years is associated with serious depression in later life [14], whereas implementing regular physical exercise training induces comparable efficacy in the treatment of major depression as antidepressant medication [15]. The described positive effects of physical exercise on mental health are accompanied by increased overall resilience [16].

Currently, there is no uniform and stringent definition of resilience [17-19]. A common psychological definition of resilience is “a person’s ability to adapt successfully to acute stress, trauma or more chronic forms of adversity” [20]. According to Kalisch et al [17], it is defined as the “empirically observable phenomenon [...] that someone does not develop lasting mental health problems although he or she is subject to adversity.” Recent resilience theories suggest a distinction to be made between resilience as an outcome, that is, the change in mental health relative to the stressor burden in a certain period, and resilience mechanisms, that is, variables that directly affect resilient outcomes [17]. By now, several psychosocial characteristics of a resilient phenotype (eg, lower levels of denial, avoidant coping behavior, and high positive emotionality) and multiple ways of promoting it (eg, improving problem-solving and planning skills) have been described [16]. Emotion regulation ability is considered a potential resilience mechanism and finds prominence in dynamic resilience theories [17,21]. Previous cross-sectional studies have indicated a positive relationship between physical activity and emotion regulation [22,23]. However, the driving neural circuits and underlying molecular pathways in resilience, especially in the context of physical exercise, are only beginning to be unraveled [16].

The major neuroendocrine and neural drivers of the responses to stress are the hypothalamic-pituitary-adrenal (HPA) axis, which mediates glucocorticoid (cortisol) release, and the sympathetic nervous system, which initiates the release of catecholamines (epinephrine and norepinephrine) in interaction with the immune system. Adequate activation of these systems in response to psychological or physical stress and subsequent restoration of homeostasis is critical to physical and mental health [16,24]. Malfunction of this responsive orchestration is associated with the development of several chronic diseases, including psychiatric diseases, autoimmune diseases, and cardiovascular diseases, contributing to mortality worldwide [25-27]. Acute bouts of physical exercise activate the HPA axis and the sympathetic nervous system, leading to increased stress hormone release followed by immune cell mobilization in a dose-responsive fashion [28-30]. When cessation of the physical stressor and the ensuing reconstitution of a homeostatic state occurs after a moderate period, adaptive mechanisms may result in improved stress reactivity. These adaptations include neurogenesis, improved synaptic plasticity and neuroprotection (eg, by increased levels of brain-derived neurotrophic factor [30,31]), and the promotion of an anti-inflammatory state (eg, by enhanced anti-inflammatory cytokines and reduced c‑reactive protein release [32]). Consequently, regular physical exercise may increase resilience by promoting a more adaptive activation of the HPA axis. Similarly, an exercise-induced shift in the tryptophan pathway, resulting in decreased kynurenine and increased kynurenic acid plasma levels, is considered to promote neuroprotection and resilience [33,34]. Furthermore, physical exercise activates the endocannabinoid system, which is considered to result in cognitive benefits and an antidepressant effect [35-37]. Thus, exercise prescription constitutes a useful means for the prevention and treatment of psychological and neurodegenerative diseases and moreover offers the possibility to enhance resilience in the general population.

Structured physical exercise interventions have been successfully implemented to improve disease states in brain diseases, such as major depression, Alzheimer disease, and Parkinson disease [15,38,39]. However, personalized training in a face-to-face fashion requires a high workload for coaches, and participants need to adhere to a strict time schedule. Individualized web-based physical exercise interventions allow trainers to remotely supervise multiple participants in a time- and cost-effective manner, for example, by providing weekly feedback. In turn, participants are highly flexible when integrating the training sessions into their daily routines and still receive individualized training programs from a coach. Our research group had previously shown in different types of patients that a web-based exercise program is useful, does not harm any participant, and improves physiological parameters, such as VO_2_peak [40,41], and clinically relevant parameters [42-45].

Physical activity is positively associated with blunted stress reactivity and shorter stress recovery in response to various stressors [46,47]. To investigate acute stress reactivity and recovery in a psychophysiological laboratory, an experimental paradigm that significantly induces stress at the psychological and physiological levels is needed. Dickerson and Kemeny [48] identified several elements that reliably elicit significant HPA axis responses in participants: (1) physical stressors (eg, heat or cold), (2) mental challenges (eg, arithmetic tasks and working memory tasks), and (3) social evaluation (eg, giving a speech in front of a jury). In psychological stress research, there are several established stress paradigms that make use of these elements. The Socially Evaluated Cold Pressor Task (SECPT) [49] and the ScanSTRESS-C [50] for acute stress induction are experimental paradigms that have previously been proven effective in eliciting acute stress responses at the psychological (ie, decreases in well-being), endocrine (ie, high levels of catecholamines and cortisol), and physiological (ie, higher heart rate levels) levels [50-52].

### Objectives

In this study, we implement an 8-week randomized controlled trial of a web-based, individualized physical exercise training intervention to evaluate the link between aerobic capacity and resilience in healthy untrained adults. Therefore, baseline values of performance diagnostics to determine the innate aerobic capacity (VO_2_peak) as well as emotion regulation abilities, stress reactivity, and stress recovery (saliva cortisol) as potential resilience mechanisms are estimated. We hypothesize that (1) participants with a high innate aerobic capacity will show a higher resilience to stress compared with participants with low aerobic capacity. This will be followed by 8 weeks of individualized web-based physical exercise training combining continuous and interval-type running exercises with the aim of progressively increasing aerobic capacity. After completion of the exercise intervention, performance diagnostics will be repeated to estimate the acquired aerobic capacity, as well as to assess the psychological parameter. In addition, secondary outcomes of molecular factors, including hair cortisol levels, endocannabinoids, catecholamines, cytokines, and cell-free DNA, and results of several questionnaires will be determined throughout the study. We hypothesize that (2) the exercise intervention will improve the aerobic capacity of the intervention group, which (3) will be accompanied by improvements in resilience factors. This will offer the possibility to exploratively study the underlying molecular mechanism (stress hormone release and immune reactions) in the promotion of resilience by regular physical activity.

## Methods

### Trial Design and Participants

This study is designed as a prospective randomized controlled trial with 2 phases of data collection before (baseline examination; time point 0 [T0] and time point 1 [T1]) and after (final examination; time point 2 [T2] and time point 3 [T3]) 8 weeks of web-supervised physical exercise training intervention (T1-T2; Figure 1). The multidisciplinary single-center trial is a collaboration among the Institute of Physiological Chemistry, Department of Psychiatry and Psychotherapy, Department of Clinical Psychology and Neuropsychology, and Department of Sports Medicine, Disease Prevention and Rehabilitation. The medical association Rhineland-Palatinate approved the study (July 29, 2019, ID: 2019-14305), and the study was registered with the German Clinical Trials Register (DRKS; DRKS00018078; October 2, 2019) and conformed to the standards of the Declaration of Helsinki of the World Medical Association. Administrative changes of the protocol, if needed, are minor corrections and clarifications that have no effect on the way the study is to be conducted. An amendment will be approved by the Ethics Committee Landesärztekammer Rhineland-Palatinate before implementation. This protocol follows the guidelines from the SPIRIT (Standard Protocol Items: Recommendations for Interventional Trials) [53] and the CONSORT-eHEALTH checklist (Multimedia Appendix 1) [54]. A SPIRIT diagram of enrollment, interventions, and assessments is provided in Figure 1.

**Figure 1 figure1:**
[figure not shown]
SPIRIT (Standard Protocol Items: Recommendations for Interventional Trials) diagram of enrollment, interventions, and assessments. ADS: Allgemeine Depressionsskala; ASI: Anxiety Sensitivity Index; BRS: Brief Resilience Scale; BSI: Brief Symptom Index; CERQ: Cognitive Emotion Regulation Questionnaire; CG: Control Group; CTQ: Childhood Trauma Questionnaire; ECG: electrocardiogram; ERQ: Emotion Regulation Questionnaire; GOT: Glutamate Oxalacetate Transaminase; GPT: Glutamate Pyruvate Transaminase; GSE: General Self-Efficacy Scale; HPA: Habitual Physical Activity Questionnaire; IG: Intervention Group; IPAQ: International Physical Activity Questionnaire; MDBF: Mehrdimensionaler Befindlichkeitsfragebogen; PAR-Q: Physical Activity Readiness Questionnaire; PSS-10: Perceived Stress Scale–10; SCS-D: Self-compassion Scale–German Version; SECPT: socially evaluated cold pressor test; SF-36: Short-Form Health Survey; SRS: Stress Reactivity Scale; TICS-SSCS: Trier Inventory for the assessment of Chronic Stress–Screening Scale For Chronic Stress.

The primary (VO_2_peak and saliva cortisol) and key secondary outcomes, trial methods, and designs are summarized in the World Health Organization trial registration data set (Textbox 1). This study includes 4 time points of investigation of physiological and psychological parameters, including the primary end points of a change in VO_2_peak and saliva cortisol from the baseline: at T0 and T1, baseline values will be estimated, and at T2 and T3, data collection following the control or exercise intervention will be performed. T0 and T2, as well as T1 and T3, are structured in the same way, except for the separately listed psychological examinations at the measurement points. T1 and T3 will be performed after a maximum of 10 days after T0 and T2, respectively. Written consent after a detailed oral explanation will be obtained from all participants at the beginning and after completion of the study by the responsible study physician. At the beginning of the study (T0), the participants will not be fully informed about the purpose and aim of the psychological stress tests. Full clarification will take place at T3. If a participant wishes to discontinue the study prematurely, they will be fully informed about the purpose and aim of the psychological stress tests.

Participant recruitment commenced in September 2019. Participants were and will be recruited via flyer announcements for the study (Multimedia Appendix 2) at multiple locations at the Johannes Gutenberg-University of Mainz and the University Medical Center campuses, as well as diverse places for leisure activities, as impersonal recruitment. Inclusion into the study is a two-step procedure beginning with a telephone survey according to the eligibility criteria (Textbox 2). At the first visit, sport capability will be confirmed and the participants will be included in the study. Blinding of participants will not take place. After telephone screening and recruitment, participants will be randomized (Figure 2) into the intervention group (IG) or control group (CG). The IG will participate in the 8-week sports intervention based on a combination of continuous and interval-type running exercises. Participants in the IG will be told not to engage in further high-intensity sports activities. Participants in the CG will be told not to change their daily lifestyles during the intervention period.

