### Randomization

The included participants will be randomly assigned with a 50%-50% allocation to the IG or CG. Randomization will be performed using the EXCEPT NUMBER command in Microsoft Excel. In addition, randomization will be stratified by gender with an expected ratio of 50%-50% and BMI with an expected ratio of 33% overweight (BMI ≥25) and 67% normal weight (BMI <25) to recruit CG and IG participants with homogeneous baseline characteristics.

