#### Socially Evaluated Cold Pressure Test (T0)

Stress induction at T0 will be performed by means of the SECPT [49]. The participant will be asked to immerse their nondominant hand in a pool of cold water (0-4 °C) and to keep it there if possible. During this time, the participant will be observed by an experimenter, who will keep a neutral facial expression while taking notes on a clipboard. To further enhance the social evaluation, the face of the participant will be recorded with a mock camera. The participants will be encouraged to keep their hands immersed for a maximum of 3 minutes.

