### Peak Oxygen Uptake Determination (T1 and T3)

To determine the individual VO_2_peak as the primary end point and the training areas, participants will complete a stepwise incremental running test on a treadmill (Saturn, HP-Cosmos) until subjective exhaustion is reached or general indications for stopping an exercise test according to the American College of Sports Medicine guidelines are fulfilled [59]. Maximal oxygen uptake is reached if a plateau of VO_2_ is observed within the final 2 work rates of the stepwise incremental running test [59]. Here, we have untrained participants who may not be able to reach a plateau in VO_2_ uptake. Therefore, we will use VO_2_peak and take the highest value of VO_2_. To avoid outliers, there should be no high variance around this VO_2_ value within the 4 previously taken breaths. The exercise test includes a starting velocity of 4 km/hour, a duration of each step of 3 minutes, a pause time between 30 seconds and 60 seconds, and an increase in velocity by 1.5 km/hour from step to step. To determine the lactate threshold, 20 µL of whole blood will be collected from the fingertip with an end-to-end capillary (Sodium-Heparin, EKF-Diagnostics GmbH) at rest and between the stages. Heart rate (electrocardiogram), as well as oxygen uptake and carbon dioxide release (spiroergometry), will be continuously recorded. The latter will be used to estimate VO_2_peak for IG and CG at T1 and T3. VO_2_peak at T1 will be considered as innate aerobic capacity, and VO_2_peak of the IG at T3 will be considered as acquired aerobic capacity. Absolute and relative contraindications will be defined according to the American College of Sports Medicine guidelines [59].

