### Web-Based Supervision

The training intervention described above will be accompanied and remotely supervised with the help of a web-based physical exercise training support via a website (Figure 5) [121]. In a personal appointment after the incremental stepwise running test, the participants in the IG will be introduced to the website and will receive comprehensive information about the training. External access to the website is not possible as only study participants can register. Both the introduction and the remote training supervision will be done by 1 person, which enables the coach to supervise several participants in their training process without any time constraints. Although there is no face-to-face supervision, based on the objective training session heart rate data and GPS data as well as the subjective feedback, adequate supervision can be guaranteed remotely. Participants have the possibility to get in direct contact with the coach via a message function, for example, in case of problems or uncertainties. The weekly training schedule is also transmitted in this manner. If a participant misses the feedback, a reminder is sent via email at the beginning of the following week. In a table that participants can download from the website, they will enter various medical and sports values that are therapeutically relevant after each training session. These data will be used for evaluation and for the training adjustment of the following week, as described in Figure 4. A follow-up is planned at 12 weeks (T4) and 24 weeks (T5) after completion of T3, and participants will be asked via email to complete the web-based questionnaires used at T2.

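### Unblinded participants can know their arm before the effort-dependent T1 treadmill test, because the time of randomisation is not fixed consistently and nothing withholds the arm until T1 is done

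*Protocol article*

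**What the plan says.** Trial Design and Participants describes inclusion in two steps, a telephone survey and then the first visit: "At the first visit, sport capability will be confirmed and the participants will be included in the study". It then gives the order of allocation, "After telephone screening and recruitment, participants will be randomized (Figure 2) into the intervention group (IG) or control group (CG", and states "Blinding of participants will not take place".

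The Randomization section says who is allocated: "The included participants will be randomly assigned with a 50%-50% allocation to the IG or CG". It names an Excel command and adds stratification by gender and BMI.

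The baseline is collected at two visits. At T0 the participant is examined, including height, weight, blood pressure and ECG, and does the stress test. T1 follows within 10 days and contains the treadmill test. Peak Oxygen Uptake Determination lets that test run "until subjective exhaustion is reached" (or until a general stopping indication). It does not require a plateau, and it takes the highest VO2 subject to a check on the preceding breaths. The T1 value is both the baseline for the VO2peak primary endpoint and the definition of innate aerobic capacity.

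Web-Based Supervision fixes when training is introduced: "In a personal appointment after the incremental stepwise running test, the participants in the IG will be introduced to the website". It does not say when participants learn their arm.

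**The concern.** In an exercise trial participants cannot be blinded once training starts, and the T3 test has to be done with the arm known. The baseline does not. It can be kept free of that knowledge simply by ordering the steps.

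As written, a participant may come to T1 knowing whether eight weeks of coached running or eight weeks of no change lies ahead. In a test that ends when the participant feels exhausted, and that needs no plateau to count, this knowledge can alter effort. An intervention participant who holds back at T1 would show an inflated gain. A disappointed control who holds back would show a false gain in the control arm and hide a real effect. Extra effort would act in the opposite direction in each case.

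Two things depend on a clean T1. Statistical Methods expects the arms to be equal before the intervention and tests the time-by-group interaction, so any arm-dependent shift at T1 enters the tested contrast directly. Hypothesis 1 uses the T1 value as innate capacity, so that association would be affected too.

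**Working it through.** **1. Order of events.** Two readings are possible.

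| Reading | Basis | Arm can be known at T0? | Arm can be known at T1? |
|---|---|---|---|
| A. Allocation follows the telephone stage | Trial Design and Participants: after telephone screening and recruitment | Yes | Yes |
| B. Allocation follows inclusion at the first visit | Inclusion completed at the first visit, and the included are randomised; BMI, a stratification factor, is measured at T0 | Perhaps not | Yes, for up to 10 days |

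The Abstract does not settle it. It reports 43 of 161 telephone-screened people as included, which reads as inclusion at the telephone stage. Both readings allow the arm to be known at T1, and no section shown says that it is withheld.

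**2. The plan's own sample size.** Inputs from Statistical Methods: f(V)=0.35, alpha 0.05, power 0.80, two groups, two measurements, interaction effect.
- Degrees of freedom: df1 = (2−1)(2−1) = 1, df2 = N−2.
- Noncentrality: λ = N × f(V)² = N × 0.1225.
- The smallest N with power of at least 0.80 is 67 (power 0.806), which reproduces the stated figure. At the target of 70, power is 0.823.

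**3. Scale of that effect.** With equal arms, a between-arm difference of d SDs of the change score gives λ = N × (d/2)². So f(V)=0.35 corresponds to d = 0.70.

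**4. Illustration: no true effect, arm-dependent shift b at T1 only.** b is in SDs of the change score and is an assumption, since the article gives neither that SD nor any measure of effort bias. N = 70, df = 1 and 68, λ = 70 × (b/2)².

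| b | λ | Rejection rate (nominal 5%) |
|---|---|---|
| 0.1 | 0.175 | 7% |
| 0.2 | 0.70 | 13% |
| 0.35 | 2.14 | 30% |
| 0.5 | 4.375 | 54% |

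**5. The opposite direction.** If the true effect is the planned d = 0.70 and a shift of 0.2 works against it, the net difference is 0.70 − 0.20 = 0.50. By the last row (same λ), power is 54% instead of 82%.

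**6. Who can still be protected.** Results reports 31 completers and 4 withdrawals, so 31 + 4 = 35 had started. If the target of 70 counts starters, 70 − 35 = 35 were still to start. These include 8 already counted as eligible, who may or may not already know their arm.

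**The case against.** The strongest reply is that the sequence may be sound and only tersely reported. The order of allocation is stated relative to screening, not as before T0. Figures 1 and 2, which show the schedule and the flow, are not available here and could settle it. Training is introduced only after the running test, which fits late disclosure. No size of effort bias is documented, so the rejection rates above describe an assumption.

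Much of this stands, and it limits the point. It does not remove it: the text never says that the arm is withheld until T1 is done, and introducing the website late is not the same as disclosing the arm late.

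A reader might infer more than the article supports:

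- **That the T0 stress test, and so the cortisol endpoint, is biased by knowledge of the arm.** Under reading B the arm may be unknown at T0. Strengths and Limitations also says that the two stress tests are not directly comparable, so a simple change-score argument does not carry over.
- **That on-site exclusions fall after randomisation.** This too depends on reading A. Blood pressure and ECG are taken at T0, possibly before allocation.
- **That Excel draws fail to deliver the stratified balance.** The article states stratification and does not say that the draws are unrestricted; Excel numbers can drive a blocked list. Unrestricted draws would leave the overweight share at least 15 points apart in about 19% of trials of 70, but that scheme is not the one described. The 17 versus 14 completers show nothing either way (two-sided binomial p = 0.72).
- **That effort would fall by some stated percentage**, comparable to the low end of the 3%–19% gains cited in the discussion. The article contains no such figure.

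**Conclusion.** The point holds for T1. The article does not fix consistently when randomisation happens. On both readings allocation can come before the T1 treadmill test, participants are unblinded, and nothing shown keeps the arm from them until that test is done. The test depends on effort and supplies the baseline of one primary endpoint as well as the innate capacity measure.

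The size and direction of any bias are unknown. On the stated assumptions (a shift confined to T1, an unchanged SD of change, equal arms, N = 70), 0.2 SD would raise false rejection from 5% to about 13%, or cut power for the planned effect from 82% to 54%. The sample size of 67 is reproduced and is not in question. Effects on the T0 stress test, exclusions after allocation and failure of stratified balance are not established.

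**What to change.** For everyone still to start:

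- Reconcile Trial Design and Participants with Randomization, and name the point at which allocation takes place relative to T0 and T1.
- Make the allocation, or at least disclose it, only after the on-site eligibility checks and all T1 measurements are complete, including the blood samples after the test. Making it then is the cleaner choice, because staff running T1 cannot know the arm either.
- Tell both arms at the end of the T1 visit. The introduction appointment described in Web-Based Supervision is for the intervention group only, so it cannot serve as the disclosure point for controls. The intervention group goes on to it as already planned.
- Report when those already enrolled learned their arm, including the 8 who had not yet taken part.

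One sentence on how balance within the gender-by-BMI strata is achieved would be useful but is secondary.

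The cost is a short amendment, and participants learn their arm slightly later. Training is not delayed, because its intensity ranges already come from the T1 lactate data and it is introduced after that test. The sample size does not change.
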